### Secondary outcome analysis

Similar analyses will be conducted for secondary continuous outcomes and for secondary analyses of outcomes at other time points. Binary outcomes will be analysed using logistic regression, comparing the intervention and active control groups while adjusting for site, recruitment method and ethnicity. Adjusted odds ratios with 95% confidence intervals and corresponding p values will be reported. Secondary analyses will be considered exploratory and hence the p values will not be altered to control for multiple testing. The focus of all secondary analyses will be on estimating the difference between groups with 95% confidence intervals rather than hypothesis testing.

### Methods for additional analyses (eg, subgroup analyses)

To understand any differential effects of the intervention, subgroup analyses will be conducted stratifying by prespecified variables including site, SES, ethnicity, recruitment method, weeks postpartum (at baseline), BMI (at baseline) and parity. Interaction tests will be conducted, separately, by including interaction terms within regression models. The significance level for subgroup analyses will not be reduced but will be interpreted cautiously. As recommended, all subgroup analyses will be reported.^66^

### Statistical methods to handle protocol non-adherence and missing data

The primary analysis of weight change (kg) at 12 months will be on an intention-to-treat basis.

### Interim analyses

No interim analyses are planned.

### Economic evaluation

The within-trial economic evaluation builds on the methods successfully used in the pilot economic evaluation^27^ including the identification, measurement and valuation of resource use and expenditure and quality of life/capability well-being (table 1). The economic evaluation is conducted from a UK NHS and personal social services perspective with the addition of a societal perspective applied to capture broader impacts, consistent with the UK’s NICE guidance for public health economic evaluations.^67^ Direct costs to the healthcare system include the intervention implementation costs and any follow-up service use costs. These health and personal perspectives will be assessed to investigate a broader impact of the intervention, including direct cost to participants and indirect costs. Both costs and health outcomes will be discounted at the same annual rate of 1.5% for the reference case, as recommended by the NICE public health methods guidelines.^67^ The economic analysis uses a ‘multipronged’ approach. The total and mean per participant costs for the intervention and control groups will be calculated. A sensitivity analysis will incorporate development costs. Regression analysis, controlling for baseline differences, will be used to estimate the average cost per participant and the average quality-adjusted life-year (QALY) achieved, by group. A cost–utility analysis will report cost per QALY gained over the 24-month period using the area under the curve approach.^68^ Results will be presented on the cost-effectiveness plan and 95% confidence intervals for the incremental cost-effectiveness ratio will be determined.^69^ Joint uncertainty in costs and outcomes will be represented using a cost-effectiveness acceptability curve to present the probability of the SMS intervention being cost-effective for prevailing UK ceiling thresholds for costs per QALY gained.^70^ The cost-effectiveness analysis will align with the primary outcome, by examining differences in weight and BMI and total costs between treatment groups, the incremental cost per weight gain averted will be calculated. The mean costs and effects for each trial arm will be calculated and presented along with the incremental costs and effects between arms (including 95% confidence intervals).

The within-trial economic analysis will be carried out for the 24 months follow-up and will form the primary analysis. However, this short time horizon may be insufficient to capture the total costs and benefits related to the intervention. If differences in quality of life or capability well-being are identified, the results will be extrapolated to a lifetime horizon using modelling methods.

### Monitoring and auditing

As per contractual agreements and participant consent, direct access to trial records and source documents will be granted to the Sponsor or regulatory agencies by all research staff and trial sites, for the purposes of trial related monitoring, audits and inspections. The trial is monitored and audited in accordance with the sponsor’s policy, which is consistent with the UK Policy Framework for Health and Social Care Research, and the TSC informed of the main findings of any monitoring, audit or inspection.

### Plans to give access to the full protocol, participant-level data and statistical code

The full protocol can be obtained from https://fundingawards.nihr.ac.uk/award/NIHR131509 and the statistical analysis plan is available by request from the CI. Following publication of the results, anonymised participant-level datasets and statistical code used for generating the results are available from the corresponding author on reasonable request, as assessed by the CI and PMT and subject to any necessary data sharing agreements (see the ‘Access to data’ section). Data availability will be consistent with timelines for storage of research data (see the ‘Data management’ section).

### TSC and data monitoring

The independent TSC meets face to face or online at least annually, as required, to provide trial oversight on behalf of the sponsor and funder. The TSC determine trial progression at the recruitment midpoint (see figure 1 and ‘Recruitment’ section) and primary outcome stage. As this RCT involves a low-risk health behaviour change intervention which is unlikely to raise concerns for participant safety (no evidence of harm was reported in the pilot study or in any other text message behaviour change studies), the sponsor and funder agreed that a data monitoring committee would not be convened (see the ‘Data monitoring’ section). Participant safety is a standing agenda item at each meeting, see the ‘Adverse event reporting and harms’ section.

### Project management team

The PMT is the key decision-making group consisting of the co-applicants, trial manager and PPI representative. The PMT meet online every 2–4 months to oversee the trial design, management and conduct, including monitoring participant safety, see the ‘Adverse event reporting and harms’ section.

### Trial coordinating centre

The trial is coordinated by the CI ([name]) and the trial manager (DG) in QUB. Weekly meetings between the CI and trial manager and regular meetings with site teams are held, to discuss trial activities across the five trial sites. Site Principal Investigators (PIs) are responsible for managing staff and overseeing participant recruitment and follow-up at their sites.

### Adverse event reporting and harms

Serious adverse events (SAEs) are recorded by researchers from the time of the participant’s consent into the trial until 1 month after the end of the 12-month intervention period and reported in line with GCP guidelines and the sponsor’s adverse event reporting procedures. Site PIs review SAEs within 24 hours to determine severity, relatedness and expectedness. The CI (or delegate) is informed of any event evaluated as being severe, related and unexpected, to conduct a second review. Onward reporting of any SAEs categorised as related and expected by both the PI and CI is actioned by the CI or trial manager to the sponsor and REC within 24 hours and 15 days, respectively. All SAEs are summarised and included in annual reports to the REC and reported during meetings of the PMT and TSC.

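### The SAE rule sends the CI events rated unexpected, but attaches the 24-hour and 15-day reports to events rated expected; the two sentences need reconciling

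*Protocol article*

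**What the plan says.** All of the relevant text is in the protocol article, mostly under the heading on adverse event reporting and harms. It sets out a chain of steps.

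- Site review: "Site PIs review SAEs within 24 hours to determine severity, relatedness and expectedness".
- Second review: "The CI (or delegate) is informed of any event evaluated as being severe, related and unexpected, to conduct a second review".
- Expedited reporting: "Onward reporting of any SAEs categorised as related and expected by both the PI and CI is actioned by the CI or trial manager", and the recipients and time limits follow directly: "to the sponsor and REC within 24 hours and 15 days, respectively".

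Two broader provisions surround the chain. SAEs are to be "reported in line with GCP guidelines and the sponsor’s adverse event reporting procedures", and, for routine reporting, "All SAEs are summarised and included in annual reports to the REC and reported during meetings of the PMT and TSC".

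The section on the TSC and data monitoring adds that "the sponsor and funder agreed that a data monitoring committee would not be convened", because the intervention is regarded as low risk.

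**The concern.** The second-review sentence and the expedited-reporting sentence are consecutive and plainly meant to form one procedure: the site Principal Investigator (PI) rates the event, the CI confirms or disputes the rating, and confirmed events go to the sponsor and the REC on a clock. The expectedness category is reversed between the two sentences. Events enter CI review as *unexpected*, and leave it for the sponsor and the REC only if both reviewers rate them *expected*.

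The rule that decides which SAEs are reported within 24 hours and 15 days therefore cannot be followed as written. With no data monitoring committee, this is the only expedited SAE route to the sponsor and the REC that the article spells out. The routine routes are slower: annual REC reports, project management team (PMT) meetings every 2 to 4 months, and a trial steering committee (TSC) that meets at least annually.

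There is a second, smaller mismatch. The CI trigger requires the event to be severe, and the onward-reporting sentence has no such condition.

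**Working it through.** There is no sample size, power or error-rate figure to reproduce. The check is a logical enumeration of the two triggers.

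**Inputs**, all from the section on adverse event reporting and harms:

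- The PI rates each SAE on three attributes: severe or not, related or not, expected or not. That gives 2 × 2 × 2 = 8 possible ratings.
- The CI's view matters to onward reporting on two attributes: related or not, expected or not. That gives 2 × 2 = 4 possible ratings.
- Total combinations: 8 × 4 = 32.

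**Trigger A (CI is informed).** The PI rating must be severe, related and unexpected. That is 1 of the 8 PI ratings, combined with any of the 4 CI ratings: 1 × 4 = 4 combinations.

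**Trigger B (24-hour and 15-day reports).** Both PI and CI must rate the event related and expected. Severity is not mentioned, so 2 of the 8 PI ratings qualify (severe or not), with 1 of the 4 CI ratings: 2 × 1 = 2 combinations.

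**Overlap.** All 4 combinations in A have a PI rating of unexpected. Both combinations in B have a PI rating of expected. The overlap is 0 of 32, so 0 of the 4 events that reach the CI qualify for onward reporting.

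| PI rating of a severe, related SAE | CI informed under the stated trigger? | Meets the stated condition for expedited reporting? |
|---|---|---|
| Unexpected | Yes | No, even if the CI agrees it is related and unexpected |
| Expected | No stated route | Only if the CI also rates it, which the stated trigger does not provide for |

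**With one consistent category.** If both sentences used the same expectedness term, the overlap would be 1 of the 4 combinations that reach the CI, namely the one in which PI and CI agree on relatedness and expectedness. The arithmetic is the same whichever term is adopted, so it does not show which was intended.

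**What the count assumes.** First, that the stated trigger is the only way an event comes to be rated by the CI. The text does not say so in terms, but gives no other. Second, that the PI's rating stays as first given. A PI who re-rated an event as expected after discussion with a CI of the same view would bring it within B, but the article describes no such step.

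**Search for a reconciling passage.** The sections on the TSC and data monitoring, the PMT, the coordinating centre, and ancillary and post-trial care do not restate or correct the expectedness category.

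**The case against.** The strongest reply is that this is a one-word slip in a condensed journal article, that the full protocol is available elsewhere and was not examined here, and that the same section already binds the trial to GCP and the sponsor's procedures. Those procedures may route events correctly whatever the article says. All SAEs also reach the REC annually and are reported at PMT and TSC meetings. The trial is described as low risk, with no evidence of harm in the pilot, and nothing here touches the primary outcome, the power or the estimate.

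Much of this stands. A reader might infer that no event can ever reach expedited reporting. The documents do not support that, because the general clause is a separate reporting obligation whose details are not shown, and the CI is not said to see only the events named in the trigger. A reader might also infer that this chain is the trial's only prompt safety signal. That is wrong as well: sites review every SAE within 24 hours, the CI and trial manager meet weekly, emerging safety issues are monitored with referral to the GP, and postnatal depression scores are calculated within 1 week of receipt, with letters sent at or above the threshold. Even on the literal text, a severe, related and unexpected SAE still reaches the CI.

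The point about severity also has to be put conditionally. The article defines neither severe nor serious. If severe is loose wording for serious, the gate excludes nothing. If it means intensity, a serious, related and unexpected event that the PI does not rate severe falls outside the stated second review.

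What does not stand is the suggestion that nothing needs correcting. This is a positive statement of the wrong or mismatched category, not detail left to a longer document. The general clause may bypass the contradiction but does not resolve it. The section on protocol training and deviations has staff trained on the protocol and deviations from it reported, so its explicit reporting rule should be one that staff can follow.

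**Conclusion.** The concern holds as an internal contradiction in an operative participant-safety rule. Under the explicit two-step rule, an SAE that PI and CI both rate related and unexpected has no stated 24-hour or 15-day route, and an SAE that the PI rates expected has no stated route to the CI rating that expedited reporting would require. The overlap between the two conditions is 0 of 32 rating combinations, given the two assumptions stated with the count.

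The conclusion is limited to the written rule. It is not evidence that any event has gone or will go unreported, and whether the full protocol carries the same wording is unknown. A drafting slip is the likeliest explanation, but the article does not settle which of the two terms was meant. There is no effect on the primary analysis.

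**What to change.** 1. Reconcile the two sentences with each other, with the full protocol and with the sponsor's adverse event procedure, so that the category sent for CI review is the category reported onward to the sponsor and the REC. Which category that is should come from the sponsor's procedure.
2. State whether severe in the CI trigger means serious or refers to intensity, and either carry the same condition into the onward-reporting sentence or remove it from the trigger.
3. Check the SAEs already logged against the reconciled rule, and document any that should have been reported on the expedited clock.

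The cost is a short text correction, handled through the trial's usual amendment route if the full protocol carries the same wording, and one pass through the SAE log. No new data are needed.

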### Ancillary and post-trial care

This is deemed a low-risk public health trial and no evidence of harm has been reported in text message studies for other health behaviours or in our pilot RCT, so no post-trial care is delivered. All women are given a signposting ‘useful contacts’ leaflet during trial visits advising them on relevant agencies and organisations that they might contact for support on a variety of issues, for example, bereavement. We monitor any emerging safety issues or unintended consequences and any participants experiencing such issues will be referred to their GP for appropriate treatment. This includes the onward reporting of EPDS scores of 9 or above (table 1). The EPDS is a screening questionnaire used to detect postnatal depressive symptoms and the scale guidance indicates that women with scores meeting this threshold would benefit from further clinical assessment. We calculate scores within 1 week of receiving the completed EPDS at each follow-up time point and letters are sent to the GP and the participant to inform of scores ≥9, as per PIS and consent processes.

### Personal and public involvement*

(^*^In NI, PPI means personal and public involvement due to integrated health and social care systems. The rest of the UK use ‘patient and public involvement’ also known as ‘patient and public involvement and engagement’).

PPI was integral to the pilot study with guidance received on the development of the text message libraries and all trial methods and materials, as previously reported.^27^ The design of the present trial mirrors the methods used in the pilot trial. We recruited PPI representatives from Scotland, London and Bradford to conduct a period of trial adaptation (figure 1) whereby the library of intervention text messages and trial recruitment materials underwent further PPI to ensure content was acceptable and culturally relevant for women from a range of backgrounds and ethnicities across the UK.

We have PPI representatives on our PMT and independent TSC to contribute to decision-making throughout the trial and we seek their advice on an ad hoc basis, as matters arise. PPI representatives will help shape the dissemination plan for trial results and will review dissemination materials to ensure communication of findings in an appropriate manner.

PPI work is led by the trial team and conducted and reimbursed according to NIHR guidance for involving the public in research.^71^

### Protocol amendments

The CI, in consultation with the PMT and sponsor, is responsible for the decision to amend the protocol and, in turn, for communicating substantive changes to relevant stakeholders. Substantial and non-substantial amendments are reviewed by the sponsor to determine the appropriate amendment category then submitted to the approving REC via the IRAS system for approval prior to implementation, and subsequently disseminated to participating centres (R&D offices, regulatory agencies). Version control and details of amendment history are clearly documented in the protocol and are disseminated to the trial sites, PMT and TSC members, funder and trial registries.

The current protocol is 3.0 (10 May 2023). Amendments to the protocol incorporated (1) the added mental health objectives resulting from the additional NIHR funding; (2) an increase in trial sample size (from 850 to 888 women) to allow for higher estimated pregnancy exclusion rates in more ethnically diverse populations than were originally accounted for; (3) to include processes to collect participant self-reported weight at 12 and 24 months only as a last resort in cases where it is not possible to obtain researcher-measured weight and (4) to offer a booklet summarising the intervention content to the active control group after completion of data collection at 24 months.

### Protocol training and deviations

All trial staff undergo training on the protocol, trial processes and standard operating procedures (SOPs) for which they are responsible (detailed on the site delegation log). The trial manager monitors trial activities across sites to ensure adherence and consistency to the protocol. There are no planned protocol deviations. If a deviation occurs, it is documented and reported immediately to the CI and sponsor, including corrective and preventative actions. Frequent recurrence of protocol deviations is unacceptable, requires immediate action and could be classified as a serious breach, that is, one which is likely to significantly affect the safety or physical or mental integrity of trial participants and/or the scientific value of the trial. Any breach meeting this definition is immediately reported to the sponsor, as per the sponsor’s SOP on ‘matters of non-compliance with study protocol’.

### Peer review

This trial has undergone independent, expert peer-review as part of the NIHR PHR funding process. It has also been reviewed and approved by the QUB Research Governance, Ethics and Integrity Manager, on behalf of the sponsor.

## Ethics and dissemination

### Ethical and regulatory considerations

The trial is conducted in accordance with the recommendations for physicians involved in research on human participants adopted by the 18th World Medical Assembly, Declaration of Helsinki 1964 and later revisions, the UK Policy Framework for Health and Social Care, relevant UK data protection legislation and the principles of GCP. QUB acts as sponsor for the trial and has in place comprehensive SOPs for the approval and monitoring of research. This protocol and other relevant trial documents were reviewed and approved by the West of Scotland Research Ethics Service REC 4 22/WS/0003. Correspondence with the REC is retained in the trial master file. An annual progress report is submitted to REC until the trial end. The CI will report to REC when the trial ends (or is terminated prematurely) and a final report with trial results submitted within 1 year of this.

Appropriate approvals from participating organisations for example, NHS governance approvals are obtained before recruiting via applicable routes.

### Dissemination

Dissemination plans informed by PPI and participant and stakeholder engagement will be developed and reviewed annually. A range of outputs including NIHR final report, peer-reviewed open access publications, conference presentations, policy briefings, non-academic research summaries and a draft scaling-up plan, are anticipated to be disseminated relevant for different audiences, including trial participants, postpartum women throughout the UK, healthcare professionals, service commissioners, academics, the government and public health bodies.
